### Aim and purpose

The main purpose of the project is to evaluate if adding GSH as a treatment option within the PCBH framework (PCBH + GSH) – offered only to patients deemed suitable following a brief, structured assessment – can enhance treatment outcomes compared to the core PCBH model. Patient outcomes in the research questions below include everyday functioning (primary outcome) as well as disorder-specific symptoms. The research questions are as follows:

Primary question: When comparing patient outcomes at the care model level after 12 weeks, is PCBH + GSH more effective than the core PCBH model? If not, can non-inferiority of core PCBH be established?Among the subgroup of patients deemed suitable for structured interventions in both groups, do those receiving GSH in PCBH + GSH achieve better outcomes than those receiving BI in core PCBH? Additionally, is this effect more pronounced in patients with conditions expected to require specific treatment components, such as exposure therapy for anxiety disorders, compared to those with conditions like depression and stress, where the benefits of specific treatment components are less clearly established? If not, can non-inferiority of BI be established for these subgroups?Does adding GSH to PCBH increase treatment duration or costs of care delivery? Which model is more cost-effective, considering patient benefits in relation to healthcare and societal costs?Do the care models and treatments differ in patient satisfaction, adverse events, treatment content, and which behavioral changes patients make during and after treatment?Will the protocol-based intervention of GSH decrease variation in treatment outcome compared to BI, especially when comparing patients deemed suitable for structured interventions?In BI, do patients whose therapists use techniques aligned with evidence-based strategies for the patient’s specific symptoms (e.g., exposure for anxiety) achieve better outcomes? How do outcomes differ for various subgroups of patients receiving BI under different conditions, and how do these compare to the group receiving GSH? In GSH, how do therapists’ adherence to treatment protocols impact outcomes? More broadly, how does the specific treatment content, independent of which type of intervention it is provided in, influence patient outcomes?

Additionally, we want to explore if the PCBH + GSH model is feasible for large-scale implementation in healthcare.

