##### Symptoms

Abbreviated versions of established patient-rated questionnaires for prevalent mental health disorders will be used to measure symptoms. See Table 2 for an overview, including timepoints and cut-off scores. Each scale score will be normalized to a range of 0 to 1 by dividing it by the scale’s maximum value. This normalized value will be used in two ways:

Primary symptom: Patients indicated as suitable for structured treatments (the CORE-I-BI and EXT-I-GSH groups) will have their primary symptom measure determined based on which GSH intervention is deemed most suitable for them. The stress and exhaustion areas, which are closely related and treated using the same GSH protocol, are assessed using two separate scales. The primary symptom measure is the averaged value of both scales, though they will also be analyzed separately. Patients indicated for BI (the CORE-N-BI and EXT-N-BI groups) will not have a value for this measure.General symptom index: A composite measure will be calculated by averaging the normalized scores across all symptom scales at each measurement point. To prevent the similar scales of stress and exhaustion from disproportionately influencing the overall measure, their average will be used as a single combined score in the general symptom index. AUDIT-C and the pain scale will be excluded, as substance use and pain are not targeted by the interventions.

**Table 2 Tab2:** Overview of patient questionnaires including scale origin, algorithm cut-offs, and administration timepoints

Self-report questionnaires	Origin	Algorithm cut-off	PRE	FU4	FU8	FU12	FU52
*Functioning*,* quality of life and health behaviors*							
Brunnsviken Brief Quality of Life Scale 12-items (BBQ)	PUB		X			X	X
DAily Routines for Well-being INventory 13-items (DARWIN)	CON		X			X	X
Outcome Rating Scale 4-items (ORS)	PUB		X	X	X	X	X
World Health Organization Disability Assessment Schedule 2.0 12-items (WHODAS 2.0)	PUB		X			X	X
**(Primary Outcome) World Health Organization Disability Assessment Schedule 2.0 8-items (WHODAS 2.0)**	**PUB**		**X**	**X**	**X**	**X**	**X**
*Symptoms*							
Alcohol Use Disorders Identification Test-Concise (AUDIT-C-3)	PUB	3–4^1^	X	X	X	X	X
Generalized Anxiety Disorder 2-item (GAD-2)	PUB		X	X	X	X	X
Generalized Anxiety Disorder 7-item (GAD-7)	PUB	9	X			X	X
Insomnia Severity Index 2-item (ISI-2)	PUB	4	X	X	X	X	X
Karolinska Exhaustion Disorder Scale 3-item (KEDS-3)	CON	11^2^	X	X	X	X	X

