**Exclusion of patients clearly not indicated for structured treatment for the specified conditions**: These patients are identified based on their stated reasons for seeking help, reported health issues, and clinicians’ notes in the CRF.**Evaluation of potentially suitable patients**: Patients identified as potentially suitable for structured treatment undergo evaluation using specific scoring criteria, similar to those outlined in the decision support tool described above. In brief, this evaluation includes results from the automated algorithm, AUDIT-C scores, and the 1-item pain scale. Points are assigned when patients exhibit high scores in relevant problem areas, while deductions are made for high scores in non-relevant domains or indications of substance abuse or pain that may interfere with treatment.**Further evaluation of uncertain cases**: Patients with uncertain suitability are discussed with a supervisor and undergo additional evaluation, considering factors such as education level, health habits, and language difficulties.**Final assessment for suitable patients**: Patients deemed suitable for structured treatment have their primary problem areas assessed. The most pertinent problem is identified based on the problem area with the highest score from the automated algorithm, in conjunction with the patient’s stated reason for seeking help.

A flow chart detailing the process of the retrospective assessment can be found in Supplementary materials F.

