### Data analysis plan

Due to the pragmatic nature of the study, where randomization occurs early – after patients have been identified and invited to participate, but before they are formally included in the trial – there is an increased risk of randomized participants during assessment or treatment being deemed unsuitable for both GSH and BI due to a need for specialized or primarily medical treatment. These participants will be excluded from most analyses but are expected to be randomly distributed between study arms. Another consequence of the pragmatic design is that patients may complete the pre-treatment measures up to a week after their initial visit to manage the usually very brief waiting time in PCBH. This could particularly impact within-group BI effects, as treatment begins during the first visit. To address this, a sensitivity analysis excluding late responses will be conducted, along with an analysis of missing data to evaluate its potential impact.

Several comparisons will be made to address the research questions. For research questions (1) and (3), we will conduct between-group comparisons on primary and secondary measures at the care model level, specifically comparing all participants in PCBH group with those in the PCBH + GSH group. To address research question (2), we will compare the subgroup of patients who received GSH (the EXT-I-GSH group) within the PCBH + GSH model with those who were retrospectively assessed as indicated for structured treatment but were randomized to the core PCBH arm and therefore did not receive GSH (the CORE-I-BI group). For the subgroup analysis examining whether GSH has a greater impact on conditions where the protocol is expected to have more specific effects (insomnia, panic disorder, social phobia, health anxiety disorder, and OCD) compared to conditions the effects are expected to be more general and non-specific (depression, GAD, and stress), analyses will evaluate whether patients in the former group show larger differences between GSH and BI than patients in the latter group. Research question (4) will be analyzed at both the care model and treatment type levels, as factors such as patient satisfaction, treatment content, patient behavior, and adverse events may be influenced by both the assessment and treatment strategies.

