For research questions (5) and (6), the analysis groups will be defined based on treatment rather than the model of care. It is therefore essential to clarify how comparison groups are categorized, as they do not align fully with the randomized groups. There is only one subgroup of patients that receive GSH – the patients in the PCBH + GSH arm assessed by the clinician as suitable for GSH (the EXT-I-GSH group). In contrast, patients receiving BI can be divided in several groups, all presented in Table 3. Analyses will be conducted on various combinations of patients receiving BI to account for potential differences among these groups. For example, CORE-N-BI and EXT-N-BI may present with more complex symptoms or social challenges compared to CORE-I-BI – or alternatively, they may have less complex, transient life stressors. Additionally, the diagnostic assessment in the PCBH + GSH model may influence the effectiveness of BI in either direction, necessitating comparisons between patients who received BI in the core model and those in the extended model.

**Table 3 Tab3:** Treatment-level analysis groups

	Core PCBH arm		PCBH + GSH arm	
	CORE-I-BI	CORE-N-BI	EXT-I-GSH	EXT–N-BI
**All patients receiving GSH**			X	
**All patients receiving BI**	X	X		X
**Receiving BI despite an indication for structured treatment**	X			
**Receiving BI in accordance with the indicated treatment**		X		X
**Receiving BI following an extended assessment confirming BI as appropriate**				X
**Receiving BI after the contextual interview**	X	X		

Notes. CORE-I-BI = Patients receiving brief interventions (BI) within the core PCBH model who were retrospectively assessed as suitable for structured treatment

CORE-N-BI = Patients receiving brief interventions (BI) within the core PCBH model who were retrospectively assessed as not suitable for structured treatment

EXT-I-GSH = Patients receiving guided self-help (GSH) after undergoing an extended diagnostic assessment within the PCBH + GSH model, where they were deemed suitable for structured treatment

EXT-N-BI = Patients receiving brief interventions (BI) after an extended diagnostic assessment within the PCBH + GSH model, where they were not deemed suitable for structured treatment

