The primary statistical methods employed will be Hierarchical Linear Models and Generalized Estimating Equations. Missing data will be handled using multiple imputation techniques that align with the missing data mechanism, while accounting for the multilevel structure of the data. Imputation models will be specified to reflect the underlying data structure, provided the complexity does not hinder model convergence. The analyses will consider the hierarchical structure of the data, such as nesting patients under therapists under PCCs for patient outcomes. The variance of each grouping level in the models will be calculated as the intra-class correlation (ICC) metric. An ICC > 0.10 will be used as a cutoff for the relevance of including it in the final model.

The non-inferiority analysis will be conducted by estimating the mean differences and standard errors at FU12, using Rubin’s rule after performing multiple imputations for missing data. A one-sided 95% CI (corresponding to a 90% two-sided CI) will be calculated for the estimated mean difference. To determine the outcome, we will compare the lower bound of the confidence interval with the non-inferiority margin of *d* = 0.20. If the lower bound of the CI is above this margin, non-inferiority will be established, in line with prior recommendations [72]. For research question (4), which hypothesizes that GSH protocols with assumed specific effects may demonstrate superior outcomes compared to BI, we will include a dummy variable in the model to represent the type of GSH protocol used (specific or non-specific).

For Health Economic Analyses in question (3), effectiveness will be assessed by constructing quality-adjusted life-years (QALYs) based on EQ-5D. Incremental cost-effectiveness ratios (ICERs) will be calculated, and Monte Carlo simulation with non-parametric bootstrapping will be conducted to address the uncertainty of the ICER point estimates. Cost-effectiveness acceptability curves (CEACs) will be employed to examine cost-effectiveness across varying willingness-to-pay scenarios.

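### The model term named for the specific versus non-specific question does not match the difference-of-differences that the same section says will be tested

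*Protocol article*

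**What the plan says.** The protocol article deals with this question in three places.

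- **Aim and purpose**, within the question on patients suitable for structured treatment: "is this effect more pronounced in patients with conditions expected to require specific treatment components". The effect meant is GSH against BI.
- **Data analysis plan**, where the comparisons are set out: "analyses will evaluate whether patients in the former group show larger differences between GSH and BI than patients in the latter group". The specific class is listed as "insomnia, panic disorder, social phobia, health anxiety disorder, and OCD"; the non-specific class is depression, GAD and stress. The groups compared are EXT-I-GSH and CORE-I-BI.
- **Data analysis plan**, in the paragraph on non-inferiority: "For research question (4), which hypothesizes that GSH protocols with assumed specific effects may demonstrate superior outcomes compared to BI", followed by the model term: "we will include a dummy variable in the model to represent the type of GSH protocol used (specific or non-specific". No product with treatment is mentioned.

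Three further statements bear on how that term can be coded. On who receives GSH, the Data analysis plan says: "There is only one subgroup of patients that receive GSH", namely EXT-I-GSH. The retrospective assessment of core-arm patients ends with this step: "Patients deemed suitable for structured treatment have their primary problem areas assessed". The Symptoms section says that patients in both CORE-I-BI and EXT-I-GSH "will have their primary symptom measure determined based on which GSH intervention is deemed most suitable for them".

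**The concern.** The stated question concerns effect modification: is the GSH-minus-BI difference greater in one class of conditions than in the other? The coefficient that answers it is a treatment-by-class interaction. The term actually named is a label for the protocol a patient worked through, and BI patients worked through none.

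The sentence containing the term also restates the hypothesis as specific protocols doing better than BI. That is a simple effect within one class, not a comparison of effects between classes. It is numbered as question (4), which the same section elsewhere uses for satisfaction, treatment content, patient behaviour and adverse events.

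At stake is the trial's answer to which patients need protocol-based treatment. If the literal term were fitted and read, a difference in course between, say, insomnia and depression could pass for a specific effect of GSH, or could cancel a real one. Leaving two descriptions of one test in the plan also leaves room to choose between them after the data are seen.

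**Working it through.** **The plan's own figure.** The plan gives no figure for this question. Its overall sample size supplies a scale for the illustration and does reproduce. With d = 0.20, two-sided alpha 0.05 and 80% power, n = 2(1.96 + 0.84)²/0.20² gives 393 per arm, 786 in total; 786/0.80 = 982.5, rounded up to 983, as stated.

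**What each coding estimates.** Let FU12 means be as follows (a higher score is worse), with γ the outcome gap between classes under BI:

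| | Non-specific | Specific |
|---|---|---|
| BI | a | a + γ |
| GSH | a − d_ns | a + γ − d_s |

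- Contrast described in words: (specific GSH − specific BI) − (non-specific GSH − non-specific BI) = −(d_s − d_ns).
- Dummy for protocol used, BI coded 0, alongside treatment: specific GSH − non-specific GSH = γ − (d_s − d_ns). This is the intended contrast plus γ, so the two agree only when γ = 0.
- Condition dummy in both groups with no product term (equal groups, same class mix): γ − (d_s − d_ns)/2. With no effect modification this is pure prognosis, γ.

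**Illustration. These inputs are assumptions, not in the documents:** half of the 786 completers are indicated (786 × 0.5/2, about 196 per group), 40% of them have a specific condition, SD is 1, the GSH effect is 0.3 SD in both classes (so no true modification), and the model is a single-timepoint linear one.

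- SE of the protocol dummy = √[(1/196)(1/0.4 + 1/0.6)] = √(4.167/196) = 0.146.
- SE of the interaction = √[(2/196)(1/0.4 + 1/0.6)] = √(8.333/196) = 0.206.

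For γ = 0.2, 0.2/0.146 = 1.37, and the chance of exceeding 1.96 is about 28%. For γ = 0.4, 0.4/0.146 = 2.74, giving about 78%. Simulation with 2,000 runs per setting agrees:

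| Gap γ (SD, either direction) | Dummy-only rejects | Interaction rejects |
|---|---|---|
| 0 | about 5% | about 5% |
| 0.2 | 27–28% | 4–5% |
| 0.4 | 77–78% | about 5% |

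The average dummy coefficient equals the prognosis gap in each row.

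**The opposite error.** With true modification of 0.3 SD (d_ns = 0.2, d_s = 0.5) and γ = 0.3, the dummy has expectation 0.3 − 0.3 = 0. In simulation it averaged 0.00 and rejected in 5.5% of runs. The interaction recovered 0.30 SD, with power of about 31%.

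**Precision of the right test.** The interaction detectable with 80% power is (1.96 + 0.84) × 0.206 = 0.58 SD in this setting. It runs from 0.48 to 0.80 SD over 30–70% indicated and 30–50% specific.

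**The case against.** A reader might infer that the plan contains no test of effect modification and that its answer is bound to rest on the wrong coefficient. The documents do not support that. The Data analysis plan states the right contrast in words and fixes both lists of conditions. The sentence on the dummy says only that it enters the model; it neither rules out a product with treatment nor says which coefficient will be read. The dummy may well be meant as the moderator.

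A reader might also infer that the classification is undefined for BI patients. That is too strong. CORE-I-BI patients are given a primary problem area and a most suitable GSH intervention, so a class exists for everyone in this comparison. Only the protocol *used* has no value for them. The class is missing for CORE-N-BI and EXT-N-BI, who are outside the comparison.

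The rejection rates follow from the chosen gap, class split and group size, and vanish as a problem when the gap is zero. They come from a single-timepoint model, whereas the plan names hierarchical models and GEE. A gap already present at baseline need not carry through a longitudinal model unchanged, although a gap in rate of change would. The rates are not properties of this trial.

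Finally, exact model terms are often left to an analysis plan. That would excuse silence. Here the article does name a term, and the term does not match the contrast described earlier in the same section. The wrong question number alone would be a slip, but beside a reworded hypothesis it adds to the ambiguity.

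**Conclusion.** The point stands as an inconsistency within the Data analysis plan. The contrast described in words is a difference of differences; the only model term given, read as written, estimates something else under either coding. The literal dummy matches the intended contrast only if both condition classes have the same outcome under BI, after whatever baseline adjustment the model makes. The protocol offers no ground for assuming this. Its Background suggests the contrary, describing OCD as needing highly specific intervention and depression as responding to many approaches.

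The direction of the problem is algebraic and needs no assumed figures. Its size does: about 5%, 28% and 78% false rejection for gaps of 0, 0.2 and 0.4 SD, under the assumptions listed. Importance is moderate. This is part of a secondary question for which the plan makes no power calculation, and neither the primary analysis nor the sample size of 983 is touched.

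**What to change.** Replace the sentence on the dummy in the Data analysis plan so that it:

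1. defines condition class (specific or non-specific, by the lists already given) for both EXT-I-GSH and CORE-I-BI, from the primary problem area: the GSH protocol used in the former, the one deemed most suitable in the latter;
2. includes group, class and group-by-class in the planned model, with the time terms needed to obtain the FU12 contrast;
3. bases the answer on the FU12 group-by-class contrast with its 95% CI;
4. cites research question (2) and words the hypothesis as a comparison of GSH-versus-BI differences.

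This needs about one sentence and no new data, since the class follows from assessments already planned. The cost is candour about precision: in the setting above, the 95% CI would extend about 1.96 × 0.206 = 0.40 SD either side of the estimate, so a modest difference between classes may remain unresolved.

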## Discussion

In this study protocol, we present a comprehensive framework for evaluating the effectiveness of the PCBH + GSH model compared to the core PCHB model. Additionally, we aim to increase knowledge of which patient groups benefit most from which type of intervention as well as test an assessment model that could be integrated into standard healthcare practice. Our aim is to generally expand the evidence base for PCBH and specifically explore whether GSH can complement the treatment options. We also seek to investigate the cost-effectiveness associated with the PCBH + GSH model compared to core PCBH and evaluate several aspects related to care processes and implementation. These findings will offer valuable insights for optimizing healthcare resource allocation and mental health service delivery in primary care settings.

However, certain difficulties should be acknowledged. Conducting clinical studies within routine healthcare settings presents inherent challenges, and implementing GSH – a structured treatment grounded in the medical model – within organizations accustomed to the contextually based, pragmatic PCBH model may introduce additional complexities. This may be more pertinent during periods of time and resource constraints in the PCC. While PCBH operates under a population-based healthcare approach, marked by flexible problem-solving in the face of constraints, ESTs adheres to principles aimed at following protocols maximize treatment effects for individual patients [29]. In a PCC where both treatment options are being investigated, divergent opinions may emerge regarding the appropriate course of action when resources are insufficient: either adjusting the duration or intensity of treatment to maintain high availability or reducing availability and providing a complete GSH intervention within the timeframe. In this study, where clinicians ultimately decide whether a diagnostic assessment ends with a patient being offered GSH or not, it may also impact how many patients are offered GSH. This discrepancy could potentially impact fidelity to either the GSH protocols or the PCBH principles. These issues are considered research questions in their own right, as they could offer valuable insights into the broader feasibility of the PCBH + GSH model, in addition to posing potential threats to the internal validity of the clinical trial. Other limitations of this study, as previously mentioned, include the early randomization procedure, which occurs prior to formal study inclusion, and the potential delay in patients completing the pre-treatment measures, which may be submitted up to a week after their initial visit. Additionally, certain effects, such as whether the implementation of GSH reduces availability, cannot be fully evaluated, as each PCC offers both the core and extended models simultaneously. This limits the generalizability of the findings regarding what would occur if only one model were implemented at a given PCC.

In conclusion, the study described in this protocol represents a significant advancement in integrated mental health care delivery in primary care. Through rigorous evaluation of PCBH and a possible integration of GSH in the PCBH model, we aim to inform evidence-based practice and policy development in primary care mental health.

